At least n=50 consecutive spontaneously breathing hospitalized patients requiring a scheduled, or with deferred emergency, measurement of CVP by direct cannulation, will be also studied at bedside by means of US-JVP. In particular, a portion of this sample (n=25) will include patients affected by various cardiac pathologies (e.g. congestive heart failure, atrial septal defect, tricuspid regurgitation, atrial fibrillation, tricuspid stenosis, AV blocks, constrictive pericarditis) in order to outline different US-JVP waveforms patterns with a potential diagnostic power.

Inclusion criteria: hospitalized adult > 18 years in spontaneous breathing requiring a direct measurement of the CVP, scheduled or in a deferred emergency. Part of this sample will include patients affected by cardiac diseases (e.g. congestive heart failure, atrial septal defect, tricuspid regurgitation, atrial fibrillation, tricuspid stenosis, AV blocks, constrictive pericarditis)

Exclusion criteria: no clinical exclusion criteria. Pregnancy.

The sample size has been determined considering the potential recruitable healthy subjects and patients referred to the intensive care unit, the workload actually sustainable by the investigators and the need for the scientific aim of the research (e.g. n=50 measurements will allow obtaining a JVP waveform derived from about 6000 tracing by hand in order to refine the algorithm that is the basis of the US-JVP software automatic procedure).

Methods

US-JVP acquisition imaging: all subjects, in supine position with the neck latch on the longitudinal axis and tilted 45° backward, will undergo US scanning (B-mode images sequence) of the right and left IJVs using a probe linear array 7.5-11 MHz. After the correct image acquisition, for each neck side a clip of 30” will be recorded. US assessments will be performed by a skilled operator blinded to clinical conditions of the hospitalized patients and to subsequent measures of invasive CVP.

Estimated total time for US assessment is 5’. Immediately afterwards, in hospitalized patients, CVP assessment by direct cannulation of the venous system will be performed by competent staff operators according to the standard.

Phase 2: Full validation process of the improved US-JVP measurements

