The validation processes will include assessment of the diagnostic power of the US-JVP estimated CVP values and US-JVP waveforms, including evaluation of sensibility, specificity, predictive positive and negative values, accuracy and precision, compared to the gold standard of direct invasive measurement of CVP.

Setting

OU of Translational Surgery and OU of University Anesthesiology and Intensive care, University Hospital of Ferrara and Eco-Fluid dynamics lab of the Department of Physics, University of Ferrara.

Subjects

n= 150 consecutive hospitalized spontaneously breathing patients requiring a scheduled, or with deferred emergency, measurement of CVP by direct cannulation.

Inclusion criteria: hospitalized adult > 18 years in spontaneous breathing requiring a direct measurement of the CVP, scheduled or in a deferred emergency.

Exclusion criteria: no clinical exclusion criteria. Pregnancy,

Methods

All patients will undergo a US scanning of the neck at bedside as described above, performed independently and sequentially by two skilled operators to verify the inter-observer reliability. To verify the test-retest reliability, operators will repeat the procedure twice and two 30”clips will be recorded. Operators will be blinded to the respective evaluations, to the clinical condition of the patient and to the subsequent measures of invasive CVP. Immediately afterwards CVP assessment by direct cannulation of the venous system will be performed by competent staff operators according to the standard.

For all the phases of the study, the measurement of CVP will not be carried out for experimental purposes but will be part of the scheduled plan for each subject during the hospitalization. Only the numerical data obtained will be considered for the purpose of this study. Therefore, no variation is expected with respect to the normal diagnostic-therapeutic pathway already defined for each study subject.

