**STATISTICAL ANALYSIS**

Aim1-Phase 1. Descriptive data will be expressed as the mean ± standard deviation or median and range according to the nature of the variables.

Aim1-Phase 2. The new US-JVP method will be compared to the gold standard of invasive CVP measurement in patients from an intensive care unit, with operators blinded to the patient’s condition and values of the direct measure of CVP. The number of patients required to estimate sensitivity and specificity, in a target population with a prevalence of 50%, assuming a clinically acceptable width of the 95% confidence interval of 10%, and a sensitivity and a specificity at least both of sizes 0.80, is 123. In order to correct for missing values, we will collect 20% patients more for a total sample size of 150 (11). Correlation between the two methods (US-CVP) will be analyzed using Pearson’s coefficient. The Bland-Altman method will be used to analyze the agreement between the measurements. The validation processes will assess the diagnostic power of the US-JVP evaluating sensitivity, specificity, predictive positive and negative values, accuracy and precision. Receiver operating characteristic (ROC) curves will be used to assess the sensitivity and specificity corresponding to different cutoffs for the new US-JVP method. Inter observers and test-retest reliability will be also calculated.

Aim 2 – Phase 3. The sample size needed to assess reliability between operators is based on Walter et al. (12). Assuming a minimally acceptable level of reliability of 0.60, given an alternative hypothesis of a level of reliability of 0.80, an alpha level of 0.05, a power of 0.80, a total of 40 patients are necessary to be evaluated independently by each clinician. Intraclass correlation coefficient (ICC) will be determined.

Aim 2 – Phase 4. Intraclass correlation coefficient (ICC) will be determined after the training. The Bland-Altman method will be also used to analyze the agreement between clinicians.

The statistical approach and analysis will be followed and carried out by statisticians of the Department of Public Health, Experimental and Forensic Medicine, Unit of Biostatistics and Clinical Epidemiology, University of Pavia

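### Phase 2 is sized on one sensitivity and one specificity, but no invasive CVP value defines a positive patient and no US-JVP cut-off is fixed, so the accuracy results are open to cut-off selection in the validation sample itself

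*Protocol*

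**What the plan says.** The Protocol's STATISTICAL ANALYSIS (Aim1-Phase 2) gives a precision-based sample size. It is computed "in a target population with a prevalence of 50" per cent, with a "clinically acceptable width of the 95% confidence interval of 10" per cent, and "a sensitivity and a specificity at least both of sizes 0.80, is 123". The total is then raised for missing values: "we will collect 20% patients more for a total sample size of 150".

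EXPERIMENTAL DESIGN AIM 1 describes Phase 2 as the full validation and enrols one undivided sample: "n= 150 consecutive hospitalized spontaneously breathing patients requiring a scheduled, or with deferred emergency, measurement of CVP by direct cannulation". Diagnostic performance, including predictive values, is to be judged against invasive CVP. On cut-offs the statistical section says only: "Receiver operating characteristic (ROC) curves will be used to assess the sensitivity and specificity corresponding to different cutoffs for the new US-JVP method". Pearson correlation and Bland-Altman agreement are planned as well.

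No section gives a CVP value that makes a patient reference-positive, a US-JVP cut-off, or a rule for choosing one.

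Phase 1 already includes paired data: "At least n=50 consecutive spontaneously breathing hospitalized patients requiring a scheduled, or with deferred emergency, measurement of CVP by direct cannulation". It is also meant to yield a physical model that estimates CVP. Its planned analysis is descriptive, and no threshold is carried forward from it.

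RISK ANALYSIS, POSSIBLE PROBLEMS AND SOLUTIONS adds an interim analysis at month 12, after which the software or the physical model may be revised. The Timeline places Phase 2 in months 6 to 18, so this look falls inside the validation phase.

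**The concern.** Invasive CVP is a continuous measurement. Sensitivity, specificity, predictive values and prevalence exist only once a CVP value separates positive from negative patients. For the first three, a US-JVP cut-off is needed too. The Protocol commits to numbers for these quantities (0.80, 0.80, 50%) and derives its sample size from them without the definitions that give them meaning.

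Two things are at stake.

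- **Precision.** The sample size holds only at 50% prevalence, and prevalence depends on the CVP value eventually used. Choosing that value afterwards to obtain 50% would itself be driven by the data.
- **Optimism.** With no cut-off fixed in advance and ROC exploration in the same 150 patients, the plan leaves room to report the best-looking point on the curve as the validated accuracy. Accuracy at a cut-off selected this way is too high on average, and an ordinary confidence interval ignores the selection. The possible month-12 revision is a second route to tuning on validation data, since the Protocol does not say how patients assessed before a revision are to be analysed.

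**Working it through.** **1. Reproducing the stated sample size**

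Inputs (Protocol, STATISTICAL ANALYSIS, Aim1-Phase 2): z = 1.96, p = 0.80, prevalence 0.50, stated interval width 10%.

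Formula: N = z² p(1−p) / (W² × prevalence), where W is the half-width.

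- W = 0.10: 1.96² × 0.16 / 0.10² = 61.46 positives; 61.46 / 0.50 = 122.9, so 123. This matches.
- W = 0.05 (10% read as full width): N = 492. The stated 123 therefore uses 10 points as the half-width.
- Inflation: 123 × 1.2 = 148 and 123 / 0.8 = 154. The stated 150 lies between them.

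**2. Dependence on the undefined CVP value**

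The number of positives is N × prevalence. The Protocol gives no prevalence data, so the 30% and 20% rows are assumptions that show the range.

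| Prevalence at the CVP value used | N needed for ±10 points on sensitivity | Positives among 123 | Sensitivity half-width with 123 |
|---|---|---|---|
| 50% | 61.46/0.50 = 122.9 → 123 | 61.5 | 1.96√(0.16/61.5) = 10.0 points |
| 30% | 61.46/0.30 = 204.9 → 205 | 36.9 | 1.96√(0.16/36.9) = 12.9 points |
| 20% | 61.46/0.20 = 307.3 → 308 | 24.6 | 1.96√(0.16/24.6) = 15.8 points |

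Above 50% the same loss falls on specificity.

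**3. Optimism if the cut-off is chosen in the same patients**

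Assumptions (none is in the Protocol): equal-variance binormal marker; true sensitivity = specificity = 0.80 at the best cut-off (separation 1.683 SD); cut-off at the maximum Youden index in the sample; 8,000 simulated datasets per setting. Optimism is the apparent value minus the true value at the chosen cut-off, averaged over the two indices.

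| N (prevalence 50%) | Apparent Se / Sp | True Se / Sp at that cut-off | Optimism per index | Excess over the attainable 0.80 | Coverage of 95% CI for Se |
|---|---|---|---|---|---|
| 150 | 0.812 / 0.828 | 0.785 / 0.801 | 2.7 points | 2.0 points | about 89% |
| 123 | 0.811 / 0.835 | 0.779 / 0.804 | 3.1 points | 2.3 points | about 87% |

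- With the cut-off fixed in advance, the mean is 0.800 and coverage of the simple Wald interval is about 93% at either size. Part of the shortfall from 95% therefore belongs to the interval method, not to the selection.
- Over true values of 0.70 to 0.85, prevalence of 30% to 50%, and N of 123 and 150, optimism runs from 2.4 to 4.2 points per index. Coverage is below 90% in every setting.
- A separate run of 4,000 datasets at n=150 gave 5.7 points on the sum of the two indices, 5.7 / 2 = 2.85 each, in agreement.
- Against the planned half-width of 10 points, 2.7 and 3.1 points are 27% and 31%.

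**The case against.** A reader might infer that the headline accuracy will be taken from the best ROC cut-off and is therefore biased upward. The documents do not support that. The Protocol says ROC curves will show performance at different cut-offs. It names no Youden index, no optimal cut-off and no headline pair. A full ROC curve, or accuracy at any cut-off set beforehand, carries no selection bias. The sentence promising sensitivity, specificity and predictive values is separate and is not tied to a ROC-chosen point. This objection stands, and it makes the bias conditional.

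Three further points deserve weight.

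- **An unseen SAP could hold the cut-off rule.** That is true of the US-JVP cut-off and of any optimism correction. It does not answer the missing CVP value, because the Protocol itself fixes prevalence, accuracy and sample size, and these need that definition.
- **Validation does not rest on cut-offs alone.** Correlation and Bland-Altman agreement need none. If US-JVP yields an estimate on the CVP scale, one CVP value could serve both methods and no ROC selection would be needed. That is a good solution, but the Protocol does not adopt it.
- **The undefined CVP value does not by itself push accuracy upward.** This is correct. It leaves the target undefined and the precision unknown, which is a different fault.

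**Conclusion.** The point holds in a limited form. The Protocol sizes its validation phase on a prevalence and accuracy that cannot be interpreted without a reference-positive CVP value, and it gives none. The only cut-off method it states uses the validation patients themselves, so it cannot validate a cut-off. Whether bias results depends on what is later reported.

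If the best cut-off were reported from those data, the overstatement would be modest but systematic: about 2 to 4 points on each of sensitivity and specificity, with coverage for sensitivity below 90%. This rests on the binormal model and Youden selection; another marker distribution or selection rule would change the figures. The loss of precision if prevalence departs from 50% could be larger, but its size is unknown because the Protocol offers no prevalence data. The change should be made, although the design itself does not have to be altered.

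**What to change.** Add to STATISTICAL ANALYSIS, Aim1-Phase 2:

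1. Before the first Phase 2 patient, the investigators fix the CVP value that defines a reference-positive patient, on grounds independent of the US-JVP data. They check the 50% prevalence against the Phase 1 patients and restate the expected precision if it differs. With 50 patients the check is rough (1.96√(0.25/50) = 14 points either way), and 25 of them are recruited for cardiac disease, a quota that Phase 2 does not have.
2. The US-JVP cut-off is locked at the end of Phase 1 from the 50 paired patients, or the same CVP value is applied to the CVP estimated by US-JVP.
3. Primary Phase 2 sensitivity, specificity and predictive values use this locked pair. ROC curves and other cut-offs are secondary, and any cut-off re-chosen on Phase 2 data is reported with bootstrap optimism correction.
4. If the software or model is revised at the month-12 interim, the revised version and its cut-off are locked again. Patients used for the revision are reported separately from those assessed after the new lock.

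**Cost.** Protocol wording and a dated lock record after Phase 1. The sample size is unchanged if 50% prevalence holds. The 50 Phase 1 patients also serve to develop the algorithm, so a cut-off taken from them may be slightly suboptimal and reported accuracy a few points lower; it would still be an honest estimate for that cut-off. A mid-phase revision would leave fewer patients for the final validation estimate.

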**EXPERIMENTAL DESIGN AIM 2**

Aim 2 will be developed in 2 phases.

The transferability of the new technique will be tested in an emergency clinical setting and in a specialized one. Four clinicians without specific expertise in the use of ultrasound technique will be involved in this project. They will be asked to use the new US-JVP technique, before (Phase 3) and after specific training (Phase 4).

Setting

OU of Translational Surgery, OU Emergency Service and OU Neurosurgery University Hospital of Ferrara.

Subjects: n = 40 consecutive patients requiring an evaluation of the JVP /CVP in scheduled or referred emergency.

Inclusion criteria: patients requiring an evaluation of the JVP/CVP in deferred emergency.

Exclusion criteria: no clinical exclusion criteria. Pregnancy,

Methods

This second part of the study will involve n=4 clinicians belonging to emergency and specialized operative units, without a specific skill in US evaluations. Clinicians will receive a basic explanation about the US-JVP technique and its modality of imaging acquisition.

Phase 3: Each clinician will evaluate n=10 subjects using US-JVP technique (independently, in different times and each one in their own context). Measurements recorded (twice for each neck side for assessing repeatability and reproducibility) will be compared to those ones immediately collected afterwards by a skilled operator.

Phase 4: The whole experiment will be repeated by the same clinicians, after a specific detailed training on US-JVP technique, to evaluate any difference in accuracy and precision with respect to phase 3.

The ultrasound evaluation will be additional to the normal diagnostic-therapeutic pathway defined for the patient who will therefore not undergo any substantial variation.

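### Aim 2: the only statistic planned in both Phase 3 and Phase 4 is the ICC, which depends on patient spread and does not isolate bias, so it is a poor measure of a training effect on accuracy and precision

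*Protocol*

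**What the plan says.** The section EXPERIMENTAL DESIGN AIM 2 has four clinicians without ultrasound expertise. In Phase 3 each examines 10 subjects, separately and in their own unit. A skilled operator takes comparison readings straight afterwards. In Phase 4 the same clinicians repeat the experiment after detailed training, "to evaluate any difference in accuracy and precision with respect to phase 3". The Subjects line for the whole aim reads "n = 40 consecutive patients requiring an evaluation of the JVP /CVP in scheduled or referred emergency".

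The section STATISTICAL ANALYSIS assigns methods phase by phase:

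- **Phase 3:** the ICC only. The size comes from a single reliability test, "Assuming a minimally acceptable level of reliability of 0.60" and testing it against 0.80 at 5% alpha with 80% power, which leads to the statement that "a total of 40 patients are necessary to be evaluated independently by each clinician".
- **Phase 4:** "Intraclass correlation coefficient (ICC) will be determined after the training". Bland-Altman is added, to describe agreement among the clinicians.

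No statistic is named for the change from Phase 3 to Phase 4, and neither section says whether the Phase 4 patients are new.

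**The concern.** The objective names two properties, accuracy and precision. The ICC is the share of total variance that lies between patients, so it mixes reading error with case mix. It does not isolate bias either: a consistency ICC ignores a systematic offset, and an agreement ICC blends it with random error.

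Bland-Altman does give bias and spread in measurement units, but it is assigned to Phase 4 alone, so there is no pre-training counterpart. It is also aimed at clinician-to-clinician agreement. Under the design section each clinician examines their own 10 subjects, so no patient is read by two of the four clinicians. The pairs that do exist, clinician against skilled operator, arise in both phases and have no Bland-Altman analysis in either.

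If the before and after ICCs are set side by side, a change in patient mix could pass for a training effect, or could hide a real one.

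**Working it through.** **1. The stated 40.** Inputs from STATISTICAL ANALYSIS: reliability 0.60 against 0.80, alpha 0.05, power 0.80. Sidedness and the number of ratings per patient are not given. The Walter–Eliasziw–Donner approximation is

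k = 1 + 2(z_α + z_β)² n / [(ln C₀)² (n − 1)], with C₀ = [1 + nρ₀/(1 − ρ₀)] / [1 + nρ₁/(1 − ρ₁)].

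With n = 2 ratings, C₀ = (1 + 2 × 1.5)/(1 + 2 × 4) = 4/9 and (ln C₀)² = 0.658. One-sided, (1.645 + 0.842)² = 6.18, so k = 1 + 4 × 6.18/0.658 = 38.6, i.e. 39. This is close to the stated 40. Two-sided gives 49, and four ratings one-sided gives 22. So 40 fits one clinician and one skilled operator per patient, tested one-sided against 0.60. It is the size of a single-phase test.

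**2. Dependence on patient spread.** ICC = σ_b²/(σ_b² + σ_e²). Assume a reading-error SD of 2 throughout, so skill is unchanged. The patient SDs are also assumed; the protocol gives none of these values.

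| Patient SD | ICC | SD of paired differences |
|---|---|---|
| 4 | 16/20 = 0.80 | √(2 × 4) = 2.83 |
| 3 | 9/13 = 0.69 | 2.83 |
| 2.5 | 6.25/10.25 = 0.61 | 2.83 |

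The ICC covers almost the whole range from the protocol's target to its minimum, while the SD of the differences does not move.

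**3. What that does to a comparison.** Simulated with 40 independent patients per phase, two readings each, two-sided 5%, 5,000 runs:

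- No training effect, patient SD 1.63 times larger in Phase 4: an ICC comparison rejects 44% of the time, a variance-ratio test on the differences 4.7%.
- Real fall in error variance (ratio 2.67), patient SD 0.61 times as large: the ICC comparison rejects 5%, the variance-ratio test 86%.

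**4. Illustrative power.** The protocol plans no between-phase test and states no expected gain. Here 0.60 and 0.80 are borrowed from the single-phase test, with 40 independent pairs per phase.

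- *ICC comparison, Fisher z.* ½ ln(1.6/0.4) = 0.693 and ½ ln(1.8/0.2) = 1.099. The standard error is √(2/38.5) = 0.228, so the ratio is 0.405/0.228 = 1.78. Two-sided power is Φ(1.78 − 1.96) = 43% (simulated 43%); one-sided it is 55%.
- *Variance of differences, equal patient spread.* Error-variance ratio (0.4/0.6)/(0.2/0.8) = 2.67. With 39 and 39 df, P(F > 1.891/2.667) = 86% two-sided (simulated 86%), or 92% one-sided. Removing four clinician means leaves 36 df per phase and 83% two-sided.
- *Variance of differences, equal total variance.* The ratio is 0.4/0.2 = 2, and two-sided power is 57% with 39 df.
- *Same 40 patients rescanned.* Simulated power of the ICC comparison is 59%.

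**5. Patient count.** Four clinicians with 10 subjects each use 40 in Phase 3 alone. A repeat needs either another 40 or the same 40 again, and the Subjects line lists 40 for the aim.

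**The case against.** The best defence is that the design section already has clinician readings compared with the skilled operator's, and repeats the whole experiment after training. The paired data therefore exist in both phases, and the exact statistic could be left to an analysis plan that is not shown. Much of this stands: it would go too far to say that the Aim 2 question cannot be answered. But the protocol does more than stay silent. It allocates methods by phase, and that allocation does not match its own objective.

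A second defence is that the sample-size sentence can be read as all four clinicians examining the same 40 patients, which would give clinician-to-clinician pairs. That conflicts with 10 subjects each in separate units. Even so, agreement among clinicians would not show accuracy against the skilled operator.

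A reader might also infer stronger things that the documents do not support:

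- *That the planned comparison has 43% power where 86% was available.* No such comparison is specified, the effect is borrowed, and 86% needs equal patient spread, the very condition in doubt.
- *That Phase 4 certainly uses different patients.* Consecutive enrolment, with training between the phases, makes this likely, but the text says only that the clinicians are the same.
- *That each phase has only 20 patients.* Four times 10 in Phase 3 rules this out.

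**Conclusion.** The point stands in a limited form. The protocol sets Phase 4 the task of showing a change in accuracy and precision, yet the one statistic it assigns to both phases is the ICC. Bland-Altman is placed in one phase only and on pairs that the design section does not produce. That mismatch is in the text and does not rest on any power figure.

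The practical size depends on unstated facts. If Phase 4 patients are new, modest differences in spread can move the ICC between about 0.6 and 0.8 with no change in skill. If the same patients are rescanned, their spread is largely shared and this risk is much smaller, but the ICC still does not isolate bias.

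The power contrast is an illustration: about 43% two-sided for the ICC, against 83–86% for the differences with equal patient spread, or about 57% with equal total variance. Correction is advisable. It does not call the rest of Aim 2 into question.

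**What to change.** In STATISTICAL ANALYSIS, for both Phase 3 and Phase 4:

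- Compute clinician-minus-skilled-operator differences and report, by Bland-Altman, their mean (accuracy relative to the skilled operator) and SD (precision).
- Name the Phase 4 versus Phase 3 change in these two quantities as the training comparison, allowing for clinician. A mixed model with phase-specific residual variance is one way to do this, but is not essential.
- Keep the ICC in each phase as secondary.
- Either drop the clinician-to-clinician Bland-Altman or explain which shared patients it would use.

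In EXPERIMENTAL DESIGN AIM 2, state whether n = 40 is per phase and whether Phase 4 patients are new or the same. Reword the sample-size sentence so that it agrees with 10 subjects per clinician.

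The cost is wording and slightly more analysis. No new data are needed if 40 per phase was intended; if 40 was meant as the total with new patients in Phase 4, the recruitment figure has to be restated.

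### Phase 4 plans a Bland-Altman analysis of agreement between clinicians, but the Aim 2 design implies that no two clinicians measure the same patient within a phase

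*Protocol*

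**What the plan says.** All places are in the Protocol.

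- **EXPERIMENTAL DESIGN AIM 2, Subjects and Methods.** The sample is "n = 40 consecutive patients requiring an evaluation of the JVP /CVP". On raters: "This second part of the study will involve n=4 clinicians belonging to emergency and specialized operative units".
- **Same section, Phase 3.** "Each clinician will evaluate n=10 subjects using US-JVP technique (independently, in different times and each one in their own context"). Readings are taken "twice for each neck side for assessing repeatability and reproducibility", and they "will be compared to those ones immediately collected afterwards by a skilled operator".
- **Same section, Phase 4.** "The whole experiment will be repeated by the same clinicians, after a specific detailed training on US-JVP technique".
- **STATISTICAL ANALYSIS, Aim 2 – Phase 3.** The sample size is based on a published method for reliability studies: "Assuming a minimally acceptable level of reliability of 0.60", an alternative of 0.80, alpha 0.05 and power 0.80. The result is 40 patients, which the sentence assigns to each clinician. An ICC is planned.
- **STATISTICAL ANALYSIS, Aim 2 – Phase 4.** An ICC is planned after training, and then: "The Bland-Altman method will be also used to analyze the agreement between clinicians".

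**The concern.** A Bland-Altman analysis works on within-patient differences between two raters. The description of who measures whom gives each patient one study clinician and one skilled operator. It provides no patient seen by two study clinicians, so the comparison named for Phase 4 has nothing to work on.

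Aim 2 asks whether newly trained operators can take up the technique, and Phase 4 exists to show a change in accuracy and precision from Phase 3. Bias and limits of agreement against the skilled operator would answer that directly. The design section sets up this comparison, but the statistical section does not name it for either phase of Aim 2.

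**Working it through.** **1. Who shares patients with whom (one phase)**

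Inputs, all from EXPERIMENTAL DESIGN AIM 2: 4 clinicians, 10 subjects each, 40 patients.

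- Clinician evaluations: 4 x 10 = 40.
- Study clinicians per patient: 40 / 40 = 1.
- Possible clinician pairings: 4 x 3 / 2 = 6.
- Patients shared by any pairing: 0.
- Clinician versus skilled-operator pairs: 40 (10 per clinician), each with two readings on each neck side from the clinician.

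The zero is an inference from 4 x 10 = 40 and from each clinician working in their own context. The count is for a single phase; the Protocol does not say whether Phase 4 uses the same 40 patients or new ones.

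**2. What the sample-size sentence would require if taken literally**

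If each clinician evaluated all 40 patients, each of the 6 pairings would have 40 shared patients. Each phase would then need 4 x 40 = 160 clinician evaluations, four times the 40 in the design section. The two sections cannot both hold.

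**3. Which layout the figure of 40 fits**

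The standard sample-size formula for testing an ICC, with k ratings per patient, is

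n = 1 + 2(z_alpha + z_power)² k / [(ln C0)² (k − 1)], where C0 = (1 + k t0)/(1 + k t1) and t = rho/(1 − rho).

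From STATISTICAL ANALYSIS: t0 = 0.60/0.40 = 1.5 and t1 = 0.80/0.20 = 4. The Protocol states neither k nor whether alpha is one- or two-sided, so both were varied.

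For k = 2, one-sided: C0 = (1 + 3)/(1 + 8) = 0.444 and (ln C0)² = 0.658. With (1.645 + 0.842)² = 6.18, n = 1 + 2 x 6.18 x 2 / 0.658 = 38.6, so 39.

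| Ratings per patient, k | n, one-sided 0.05 | n, two-sided 0.05 |
|---|---|---|
| 2 | 39 | 49 |
| 3 | 27 | 33 |
| 4 | 22 | 28 |
| 5 | 20 | 25 |

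Only two ratings per patient with one-sided alpha comes close to 40. That fits clinician plus skilled operator. Four clinicians crossed on the same patients would have needed 22 or 28. Because k and the sidedness are assumptions, this supports the design-section reading but does not prove it.

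**4. Pooled versus per clinician**

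Exact one-sided F-test power with k = 2 is 0.81 for n = 40 and 0.33 for n = 10. The figure of 40 therefore serves the 40 clinician–operator pairs pooled, not a separate test for each clinician.

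**The case against.** **The sample-size sentence makes the analysis possible.** Read literally it does, and this has to be stated. But it conflicts with the explicit 10 per clinician and with each clinician working in their own context. What stands is that the fault is partly a contradiction between two sections, and changing only the Bland-Altman sentence would leave it in place.

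**The wording may simply be loose.** The phrase about clinicians may have been meant to cover clinician versus skilled operator, and the calculation above fits that. However, the design section keeps the two roles apart, so the text as written names a different comparison. If the loose meaning was intended, the fix only writes it down.

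**A later analysis plan could settle it.** It could name a different comparison, but it cannot create pairs that the design does not collect.

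Four stronger readings are tempting and are not supported:

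- *Phase 4 has no usable agreement analysis.* An ICC is also planned, with Bland-Altman added to it, and the 40 pairs with the skilled operator exist. The ICC's raters are not named; an ICC between clinicians would fail for the same reason, but one against the skilled operator would not.
- *The clinicians all work in different units.* The setting lists three units for four clinicians, so if all work in those units, at least two share one.
- *Transferability would be made to look poor by comparing clinicians across different patients.* No such analysis is proposed anywhere.
- *Agreement between clinicians can be recovered through the skilled operator as a common reference.* The Protocol does not say that one person fills that role throughout, and each clinician's mean difference is confounded with that clinician's setting and patients.

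**Conclusion.** The point holds as a mismatch between design and analysis. Under the layout in EXPERIMENTAL DESIGN AIM 2, a between-clinician Bland-Altman analysis in Phase 4 has 0 shared patients in all 6 pairings. Clinician versus skilled operator has 40 pairs per phase, 10 per clinician. This is a stated analysis that the design cannot supply, not a detail left for later.

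The conclusion assumes that the 40 patients are divided among the clinicians without overlap, which the arithmetic implies but the text does not say. If the sample-size sentence governed instead, the analysis would be feasible, but the described design would be wrong. Either way the sections need reconciling. The damage is limited: one supplementary analysis in the second aim is affected, and the main comparison for transferability can still be made.

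**What to change.** Keeping the design of 10 subjects per clinician, amend STATISTICAL ANALYSIS, Aim 2:

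1. Replace the Phase 4 Bland-Altman sentence with wording such as: *In Phase 3 and in Phase 4, Bland-Altman bias and limits of agreement will be estimated for clinician minus skilled operator, from a model of within-patient differences that accounts for neck side and repeat readings and includes a term for clinician.*
2. State that the ICC in both phases uses the same clinician versus skilled-operator pairs.
3. Correct the sample-size sentence so that the 40 patients are the total across the four clinicians, and state the number of ratings per patient and the sidedness of alpha.
4. Report clinician-specific mean differences descriptively. They rest on 10 patients each and are confounded with that clinician's setting, patients and possibly skilled operator, so they should not be presented as between-clinician agreement.

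This costs a few sentences and no new data. The downside is that the trial makes no direct claim about agreement between clinicians. If that claim is wanted, the design must have clinicians measure common patients; with all four measuring all 40, that means 160 clinician evaluations per phase instead of 40.
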